# Feasibility of a breath robot intervention to reduce sleep problems in posttraumatic stress disorder: protocol for a randomized controlled study

**DOI:** 10.1186/s40814-023-01426-8

**Published:** 2024-02-05

**Keywords:** Posttraumatic stress disorder, Breath robot, Hyperarousal, Sleep problems, Stress symptoms, Randomized controlled trial, Pilot study

## Abstract

**Background:**

Many patients with posttraumatic stress disorder (PTSD) suffer from sleep problems. Robot-based interventions might be an innovative approach to reduce sleep problems and hyperarousal in PTSD. However, the feasibility and effectiveness of a breath robot in patients with PTSD have never been empirically tested. The aim of this study is to investigate the feasibility of a breath robot to reduce sleep problems and hyperarousal in patients with PTSD.

**Methods:**

This randomized controlled feasibility study will include *N* = 30 adult patients with at least subsyndromal PTSD (PTSD Symptom Scale – Interview-5 (PSSI-5)) according to the Diagnostic and Statistical Manual of Mental Disorders, 5th Edition (DSM-5) and impaired sleep quality (Pittsburgh Sleep Quality Index (PSQI) > 5). Patients with organic sleep disorders or currently in psychotherapeutic treatment are excluded. Study participants are randomized to receive either a 4-week Somnox 2 robot intervention including simulation of human breath or a 4-week Somnox 2 robot intervention without human breath simulation. The primary outcome will be the proportion of randomized participants providing outcome data at post-treatment. We consider a proportion of > 50% to indicate feasibility. Additional feasibility outcomes include eligibility rate, recruitment speed, uptake, retention, treatment adherence, and dropout. Potential outcomes of effectiveness (sleep quality, PSQI; severity of PTSD symptoms, PSSI-5) will be assessed at two time points, before (T0) and after (T1) the intervention. Sleep characteristics (Consensus Sleep Diary (CSD)) are measured daily.

**Discussion:**

This study is the first to investigate the feasibility of a novel breath robot intervention for reducing sleep problems and hyperarousal in PTSD patients, with effectiveness considered as a secondary outcome. If feasible and effective, the use of a breath robot could be a nonintrusive and flexible intervention to supplement psychotherapy or to bridge treatment gaps.

**Trial registration:**

DRKS, DRKS00031063. Registered on 10/012023.

## Introduction

One-third of the general population experiences a potentially traumatic event such as a car accident, rape, or physical abuse at least once in their life [23]. Approximately 12% of those affected develop posttraumatic stress disorder (PTSD), a severe mental disorder associated with psychological, social, and functional impairments [23]. Patients with PTSD show constantly increased stress levels and hyperarousal [6], both of which are associated with sleep disruptions [2]. Eight out of ten patients have difficulty falling or staying sleeping [6]. PTSD is therefore linked to greater sleep latency, sleep fragmentation, and night-to-night sleep variability, as well as to reduced sleep efficiency (for an overview see [14]). Such sleep problems associated with PTSD impair mental health [13] and quality of life [8, 26].

Slowing the breath can reduce stress in PTSD patients by affecting the autonomic nervous system [24]. Breathing techniques are regularly applied in the psychological treatment of PTSD to promote relaxation and reduce hyperarousal. While evidence-based psychotherapies exist for PTSD-related sleep problems [30, 31], their availability is limited [18]. In Germany, approximately 40% of the patients in need of psychotherapeutic treatment wait longer than 6 months before they start treatment [11]. The application of robot-assisted interventions may help to reduce these treatment gaps. Compared to psychotherapeutic treatment, robotic interventions require less time, space, and staff. Social robots that interact with humans could replace or enhance psychotherapeutic interventions [7, 9]. Robotic interventions could be used as an adjunct to psychotherapy or to bridge waiting times. However, robots have not yet been used in PTSD treatment.

First, research is needed to examine the feasibility and effectiveness of robotic breath interventions on sleep problems in PTSD patients. Therefore, the primary aim of this study is to examine the feasibility of using a breath robot (Somnox 2) in patients with PTSD. The secondary aim is to examine the potential effectiveness and the users’ experiences with the breath robot intervention to reduce sleep problems and hyperarousal.

## Methods

### Trial design

The study is a randomized controlled, investigator-blinded feasibility study with two groups. After study inclusion, participants are randomly assigned to a 4-week breath robot intervention group (active treatment: daily use of a robot stimulating human breathing) or a control group (sham treatment: daily use of a robot without breathing stimulation).

### Study setting

The study is conducted at the Institute of Clinical Psychology and Psychotherapy at the Department of Psychology at MSH Medical School Hamburg. Participants will be recruited from psychotherapeutic outpatient units and via announcements on widely accessed websites (e.g., eBay Classified Ads).

### Study procedure

Potential participants are invited by the research personnel to attend an eligibility assessment at one of two study locations of MSH Medical School Hamburg. The study personnel inform interested participants about the study and the procedures and provide the opportunity to ask questions. Potential participants receive a study sheet that provides information about the study objectives, study procedures (treatment and assessment), eligibility criteria, random allocation process, type of treatment (including benefits and risks), compensation for study participation, right of study withdrawal, data flow and security, and contact information. Subsequently, potential participants participate in a 2-h baseline assessment (T0), during which the study staff review the eligibility criteria and assess the baseline data. Eligible participants who agreed to participate sign the informed consent for the study. The study staff instruct participants on how to use the sleep robot, the technical equipment to measure digital biomarkers, and how to complete the daily sleep assessments. During the 4-week study period, participants apply the robot for at least 30 min daily before bedtime and, if possible, throughout the day. Participants will be instructed to complete the sleep diary (CSD) daily on a smartphone no later than 1 h after waking. To collect digital biomarkers, participants are instructed to wear the (EmbracePlus; [10]) day and night, except when the device needs charging. A research assistant calls the participants once a week to provide support in using the breath robot and wearable device and to clarify questions, if needed. Post-treatment (T1), the participants attend a 2-h assessment with the study staff to reassess the variables measured at T0 (Fig. 1).

**Fig. 1 Fig1:**
[figure not shown]
Schedule of enrollment, intervention, and assessment. Notes : ERQ, Emotion Regulation Questionnaire; PHQ-4, Patient Health Questionnaire-4; PSSI-5, PTSD Symptom Scale – Interview for DSM-5; PSQI, Pittsburgh Sleep Quality Index; WHO-5, World Health Organization Well-Being Index; PSS-10, Perceived Stress Scale-10; CSD, Consensus Sleep Diary; EDA, electrodermal activity; PRV, pulse rate variability; RR, respiratory rate; PR, pulse rate; MI, movement intensity; ST, skin temperature; SD, sleep detection

### Participants and eligibility criteria

Participants are included according to the following criteria: (1) 18 years of age or older; (2) diagnosis of at least subsyndromal PTSD (i.e., trauma exposure as defined in criterion A of the DSM-5 PTSD diagnosis, probable PTSD (PSSI-5 cutoff ≥ 23)), at least one intrusion symptom and one arousal / reactivity symptom (PSSI-5); and (3) impaired sleep quality (PSQI > 5). Participants are excluded according to the following criteria: (1) organic sleep disorder (e.g., sleep apnea, narcolepsy, restless legs syndrome) and (2) participation in psychotherapeutic treatment during the study period, except for the initial psychological consultations or probationary sessions to plan psychotherapeutic treatment.

### Intervention

The Somnox robot [33] was developed at the Robotics Institute of the Delft University of Technology in the Netherlands to improve sleep. The current version, Somnox 2, has the form of a bean-shaped cushion to hug and simulates human breathing (Fig. 2).

**Fig. 2 Fig2:**
[figure not shown]
The Somnox 2 sleep robot. Note : Copyright 2023 by Somnox. Used with permission

Somnox 2 is designed to reduce the user’s breath rate. When hugging, the robot detects the breath rate of the user and simulates a human breath with a slightly lower rate compared to the user. It is assumed that the users synchronize their breath with the breath of the robot. The aim of the robot breath intervention is to slow down breathing to promote relaxation and thus good sleep.

The participants of the intervention group are instructed to hold the sleep robot in their arms (i.e., to create physical contact) so that the breathing of the robot can be sensed (Fig. 2). They receive written and verbal instructions on how to use the robot and its functions. The robot has a soft surface that is pleasant to touch. The participants have the choice to adjust the breathing settings (e.g., breath rate) manually via the Somnox mobile app while using the Somnox 2. They have the option to play soothing music or nature sounds via the app. Over the 4-week period, participants are asked to hug the robot daily for at least 30 min in bed until they fall asleep and to resume this after any unwanted awakenings before sleeping. They are also instructed to use the robot whenever they like throughout the day.

### Control group

The participants in the control group are instructed to use the robot daily for at least 30 min in bed until they fell asleep and to resume this after any unwanted awakenings before sleeping. They are also instructed to use the robot whenever they like throughout the day. In the control condition, the breathing and relaxation music functions of the Somnox 2 are deactivated.

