Another strength of this study is the inclusion of a control group. We investigate the effectiveness of the daily use of a breath robot with the daily use of the same robot without breath simulation. Such a study design allows us to investigate whether the breathing of the robot  – which is assumed to be the main mechanism of action  – is crucial for the effect of the robot intervention, if present. However, this study design cannot provide information about whether the overall robot intervention, including daily hugging of the robot with a nice texture, perception of the robot’s breathing, and listening to relaxing music, will more greatly reduce sleep problems in PTSD patients compared to no intervention.

Although both study groups receive a similar intervention and instruction, participants cannot be blinded to whether the robot is breathing. The study is therefore susceptible to participant effects. However, the study personnel assessing the results are blinded, as is the person performing the statistical analysis. Another shortcoming of this study could be seen in the fact that 30 participants are too few to detect small effects. However, this study is primarily designed to assess feasibility and not to detect intervention effects. We also followed recommendations for determining sample size in pilot trials [3, 34]. The study is further limited to examining the feasibility and effectiveness over a 4-week period, as we do not conduct follow-up measurements.

Despite these limitations, we assume that this feasibility study will gain novel insights into the application of a breath robot in PTSD patients with sleeping problems. As no previous study has been conducted on this research question, it is unclear whether patients with PTSD will accept the intervention and whether the intervention will have any positive or negative effect on sleeping problems or arousal. However, if the breath robot will be feasible and effective in this patient group, the intervention has the potential to significantly improve the treatment of PTSD. Given the shortage of psychotherapy and the often long wait times for psychotherapy, it is critical to develop alternative treatment options. Breath robots such as the Somnox 2 may be more readily available, cost less, and can be used more flexibly at home compared to psychotherapy. However, based on current empirical knowledge, there is no evidence that breath robots are effective in reducing sleep problems in patients with PTSD.

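### The arms differ in optional audio as well as breathing, so the effectiveness contrast cannot show whether breathing itself is crucial, as the Discussion says the design can investigate

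*Protocol article*

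**What the plan says.** The Intervention section gives the active arm the breathing function and an audio function: "They have the option to play soothing music or nature sounds via the app". The Control group section removes both breathing and music: "In the control condition, the breathing and relaxation music functions of the Somnox 2 are deactivated". It does not mention nature sounds.

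Elsewhere the contrast is described as breathing alone. Trial design has a "control group (sham treatment: daily use of a robot without breathing stimulation". The Discussion compares daily use of a breath robot "with the daily use of the same robot without breath simulation". The Abstract, Primary outcome and Randomization sections use similar labels.

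The Discussion presents the control group as another strength and draws an inference from it: "Such a study design allows us to investigate whether the breathing of the robot", described as the assumed main mechanism, "is crucial for the effect of the robot intervention, if present". It then concedes that the design cannot compare the whole package, in which it counts relaxing music, with no intervention. It does not say that music also differs between the two randomised arms.

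**The concern.** A sham arm supports a statement about one component only if that component is all that separates it from the active arm. Here a second component, bedtime audio, is available on one side and switched off on the other. The documents' own account of the overall intervention names music separately from perceiving the breathing, so it cannot be folded into the breathing function.

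What is at stake is interpretation of the secondary aim. Cohen's d and confidence intervals are planned for the outcomes, and the sample size is justified partly by its use in planning a future trial. A between-arm difference in sleep quality, PTSD symptoms, diary variables or biomarkers would be read, on the protocol's own authority, as evidence about breathing. A later trial could then be built on that reading.

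**Working it through.** The plan gives no figure to reproduce. The check compares the arms component by component and then asks what the randomised contrast identifies.

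**Components by arm**

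| Component | Intervention arm | Control arm |
|---|---|---|
| Daily use of the robot in bed, at least 30 min | yes | yes |
| Breathing | on | off |
| Relaxation music | optional | off |
| Nature sounds | optional | not stated |

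The sources are the Intervention and Control group sections. The user's control over breath rate, also in the Intervention section, belongs to the breathing row and is not counted separately.

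**What the contrast estimates**

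Let B be the effect of breathing, M the effect of audio, and u the extent of audio use in the intervention arm, from 0 to 1. Assume that the effects add and that the control arm has no audio. Then:

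expected difference (intervention − control) = B + u·M

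- u = 0 (nobody plays audio): the difference is B.
- u = 0.5: the difference is B + 0.5·M.
- u = 1 (full use): the difference is B + M.

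The contrast equals B only if u = 0 or M = 0. The documents give neither quantity, so the distortion u·M cannot be sized from them. If effects do not add, the contrast is the joint effect of breathing and whatever audio was used, which still is not B.

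**Whether anything in the plan separates B from M**

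- There are two arms, with no breathing-only or audio-only arm, so randomisation cannot separate them.
- Participants choose audio after randomisation. Comparing users with non-users inside the intervention arm would not be a randomised comparison.
- The adherence measures under Secondary outcomes are the proportion of days of robot use and average daily minutes. Audio use is not named.
- The qualitative interview at T1 covers mechanisms of action. It may give hints about audio but cannot apportion the effect.

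**What is not touched**

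The primary outcome is the proportion of randomised participants providing T1 data, with the same threshold of more than 50% in both groups. It makes no statement about breathing. Uptake and retention are defined within the intervention arm, so they are not contrasts either.

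**The case against.** The strongest reply is that this is a feasibility study. The primary outcome is data completeness, effectiveness is secondary, the analysis is descriptive, and the Discussion says the study is not designed to detect intervention effects. That stands, and it limits the weight of the point.

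It can also be said that the audio difference is disclosed in the Control group section and that the phrases used elsewhere are short labels for an arm specified there. This is fair for the labels. It does not rescue the Discussion, which draws an inference that the specified arms cannot support and lists limitations without this one. The wording there is cautious (the design allows investigation, and the effect is conditional on being present), but calling breathing crucial is still an attribution.

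Precision is a further reply. With 15 per arm, the approximate 95% half-width around a d near zero is 1.96 × √(2/15) = 0.72, so a modest audio effect would be lost in the noise. That is true if all 30 provide data, and the interval widens if fewer do. But a wide interval does not change what the estimate is an estimate of.

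A reader might go further and infer any of the following. The documents support none of them.

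- *Audio carries over in full into the apparent breathing effect, or accounts for all of it.* Audio is optional, its uptake is not given, and no audio effect size is stated.
- *The app's adjustable settings are a further confounder.* What participants may adjust is the breathing itself: "The participants have the choice to adjust the breathing settings (e.g., breath rate) manually via the Somnox mobile app while using the Somnox 2".
- *The feasibility result is compromised.* It does not rest on the contrast.

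**Conclusion.** The point holds for the secondary effectiveness outcomes. The two arms, as configured, differ in breathing and in optional audio, and the between-arm difference estimates B + u·M. The Discussion therefore claims for the design a property it lacks, and it does not acknowledge the audio difference. The size is unknown: u lies between 0 and 1, M is not given, and the distortion vanishes if audio is not used or has no effect. The formula assumes additive effects; the failure to isolate breathing does not. Comparing a full-function device with an inactive one is a legitimate package comparison, so the fault lies in the attribution and not in having this control. It is a correction to interpretation and reporting, not a threat to the trial's main conclusion.

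**What to change.** Reconcile the Intervention and Control group sections with the Trial design and Discussion:

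1. Describe the contrast as breathing plus optional audio versus neither.
2. Limit the Discussion's attribution statement accordingly, and add the audio difference to the limitations.
3. State whether nature sounds, as well as relaxation music, are off in the control arm.
4. Record audio use in the intervention arm and report it descriptively beside the effect sizes.

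The primary outcome needs no rewording. The cost is a few sentences and one extra item of data. The claim becomes less specific, and audio use reported for participants already treated may be incomplete or recalled.

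An alternative, if the investigators choose it, is to put audio in the same state in both arms for participants not yet randomised and to record which version each participant received. The contrast among those participants would then isolate breathing. The downside is real: the trial is ongoing with N = 30, so this would leave mixed versions within arms of about 15. Which configuration to use is for the investigators to decide.

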### Outcomes

#### Primary outcome

We evaluate the feasibility of the outcome data collection, focusing on randomized participants providing data at post-treatment (T1) after a 4-week Somnox 2 robot intervention with human breath simulation, or after a 4-week Somnox 2 robot intervention without breath simulation. Feasibility, set at > 50%, applies equally to both groups. This criterion considers potentially high dropouts in individuals with mental health conditions and the technical complexity of the study (e.g., using a wearable for 4 weeks).

#### Secondary outcomes

##### Feasibility

Eligibility rate (proportion of included participants out of all screened individuals), recruitment speed (number of participants recruited in 6 months), uptake (proportion of participants who started the robot intervention out of those randomized in the intervention group), retention (proportion of participants in the intervention arm that received at least 20 robot sessions), treatment adherence (proportion of days the robot was used, average daily robot use in minutes), and dropout rate (rate of participants who were randomized but terminated study before completion of T1).

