### Sample size

We will include *N* = 30 participants. Given that the primary study aim is to assess feasibility, no formal sample size calculation was conducted, aligning with the recommendation that feasibility studies do not require sample size estimates [19]. The number of participants was limited to *N* = 30 since this is the minimum sample size needed to estimate a parameter for testing group differences [3]. This sample size meets the recommendation from Whitehead et al. [34] of a minimum of 15 participants per group when estimating the variance for a sample size calculation for a future trial designed with 90% power, two-sided 5% significance, and a medium (0.5) effect size. Interim analyses are not planned.

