### Randomization

The allocation schedule for the random assignment of the individuals to two groups was generated by the randomization software DatInf RandList version 1.2 by a researcher not involved in other parts of the study. The generation of the randomization sequence took place prior to the recruitment of participants. *N* = 30 participants are randomly assigned to one of the two groups (i.e., robot intervention with breath simulation versus robot intervention without breath simulation) in a ratio of 1:1 using permuted blocks of random sizes between 2 and 6. Each random number is separately stored in a sequentially numbered, opaque and sealed envelope. Only the unblinded research assistant responsible for the randomization has access to the randomization envelopes. After the eligibility of a participant for the study has been ensured, the participant is included in the study by a research assistant, and the next available randomization number is assigned to the participant in an ascending order.

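### The outcome named eligibility rate is included over screened, so it multiplies eligibility by consent, and no listed outcome separates the two

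*Protocol article*

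**What the plan says.** The feasibility list under Secondary outcomes fixes the first measure as "Eligibility rate (proportion of included participants out of all screened individuals".

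Study procedure describes how a person comes to be included. At the T0 visit there is an assessment "during which the study staff review the eligibility criteria and assess the baseline data". The next step is agreement: "Eligible participants who agreed to participate sign the informed consent for the study". Randomization puts it more briefly: "After the eligibility of a participant for the study has been ensured, the participant is included in the study by a research assistant". That section does not mention refusal, but neither does it remove the agreement step.

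The other feasibility measures in the same list begin later or have no denominator:

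- Uptake: "uptake (proportion of participants who started the robot intervention out of those randomized in the intervention group".
- Retention and treatment adherence concern use of the robot, so they begin after allocation.
- Dropout: "dropout rate (rate of participants who were randomized but terminated study before completion of T1".
- Recruitment speed is a count over six months.

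The article states no expected value, target or progression rule for the eligibility rate.

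**The concern.** The name and the definition do not match. Someone who meets every criterion and then says no stays in the denominator and is missing from the numerator, exactly like someone who fails a criterion. The measure cannot tell these two people apart, and no other listed measure counts the first one.

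The distinction matters here because feasibility is the primary aim and the Discussion says that acceptance by patients with PTSD is an open question. Candidates are told about random allocation and the type of treatment before T0, and one arm uses a robot with breathing and music switched off. An eligible person who declines at that point gives direct evidence on acceptability. The defined measure would file that evidence under eligibility.

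The consequences for a later trial also differ. Few eligible people would point to the entry criteria or the recruitment sources. Many eligible people declining would point to the intervention, the comparator or the burden of the study.

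**Working it through.** **Inputs from the article.** The numerator is the number included, planned at 30. Sample size refers to "a minimum of 15 participants per group when estimating the variance for a sample size calculation for a future trial designed with 90% power", and 2 × 15 = 30 reproduces the planned N. No eligibility or consent figure is given, so there is no stated rate to reproduce.

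**Assumed inputs.** Let e = eligible/screened and c = agreed/eligible. Both are assumptions, shown over a range.

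**Identity.** Included means eligible and agreed, so

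included/screened = (eligible/screened) × (agreed/eligible) = e × c.

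The shortfall against true eligibility is e − e × c = e(1 − c).

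**Shortfall in percentage points:**

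| c | e = 0.3 | e = 0.5 | e = 0.7 |
|---|---|---|---|
| 1.0 | 0 | 0 | 0 |
| 0.9 | 3 | 5 | 7 |
| 0.8 | 6 | 10 | 14 |
| 0.6 | 12 | 20 | 28 |
| 0.5 | 15 | 25 | 35 |

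**Example in counts.** Suppose 60 are screened, 40 are eligible and 30 agree. The article's measure is 30/60 = 50%. Eligibility is 40/60 = 66.7% and consent is 30/40 = 75%; 0.667 × 0.75 = 0.50.

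**One reported value, several explanations.** A reported 30% arises from each of these pairs (e, c): (0.3, 1.0), (0.5, 0.6), (0.6, 0.5) and (1.0, 0.3). In the first, all loss comes from the criteria; in the last, all loss comes from refusal.

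**Does the ratio mislead the planning of screening numbers?** Take an illustrative later trial with the parameters named under Sample size: 90% power, two-sided 5%, effect size 0.5. The usual normal formula gives 2 × (1.960 + 1.282)² / 0.5² ≈ 84.1, hence 85 per arm and 170 in total. The number to screen is 170/(e × c) = 170/0.30 = 567 for all four pairs. Dividing by e alone would give:

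| e | c | Needed: 170/(e × c) | Using e alone: 170/e |
|---|---|---|---|
| 0.3 | 1.0 | 567 | 567 |
| 0.5 | 0.6 | 567 | 340 |
| 0.6 | 0.5 | 567 | 284 |
| 1.0 | 0.3 | 567 | 170 |

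For this purpose the product is the right quantity, and eligibility alone would plan too few whenever anyone refuses. The ratio is useful but carries the wrong name.

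**The case against.** **The numerator and denominator are stated, so every reader knows what is reported.** This stands. A reader might infer that the figure is uninterpretable, or that it will misguide the next trial's screening target. The article does not support either inference: the ratio is a well-defined yield and the correct multiplier for screening load.

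**Understatement is not certain.** This also stands. If every eligible person agrees, the ratio equals true eligibility, and nothing in the article says how many will decline.

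**Unwilling people can leave before T0.** Interested people receive the study sheet beforehand, so those put off by the design may never reach the eligibility review. If such people are not counted as screened, c may be close to 1. This limits the size of the shortfall, but it does not rescue the list of outcomes: early refusal would then appear in no measure at all. If they are counted as screened, the mixing is larger.

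**An article leaves screening logs and reasons for refusal to fuller documents.** That is fair, and their absence is not the point. The point is a definition that the article does state, attached to a name that it does not fit.

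**Consent timing.** A reader might infer from the order of sentences under Study procedure that interview data are collected before written consent and that the signature should be moved earlier. The article does not support this. It condenses the procedure, its sentence order need not be a strict chronology, and it does not exclude an earlier agreement to screening. Moving consent ahead of the eligibility assessment would also leave the eligibility of those who refuse unknown, which is the information wanted here.

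**Conclusion.** The point holds in limited form. The measure called the eligibility rate is eligibility times consent. It lies below true eligibility whenever any eligible person declines, by e(1 − c), and it cannot show whether people are lost to the criteria or to unwillingness. No other listed feasibility outcome recovers refusal before randomisation.

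The percentage-point figures rest on assumed values of e and c; only the identity and the absence of a separate refusal measure rest on the article itself. The effect is confined to one descriptive secondary outcome with no threshold attached. The primary outcome, the proportion of randomised participants with T1 data, starts after the step in question and is unaffected, as is N = 30. It is still worth correcting, because rates of this kind are a main product of a feasibility trial.

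**What to change.** Replace the single measure with three, each reported with its counts and a 95% confidence interval:

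- eligibility rate = eligible/screened;
- consent rate = randomised/eligible;
- overall recruitment yield = included/screened, which is the present ratio under a name that fits it.

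Add a sentence saying at which step a person counts as screened, and show people who withdraw before their eligibility is known as a separate count, so that they are classed neither as ineligible nor as eligible refusals.

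The cost is a change of wording and one column in the screening log that separates not eligible from eligible but declined. No visit, assessment, sample size or primary analysis changes. The column should be filled in while screening is under way, because the distinction is hard to reconstruct afterwards.

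### Recruitment speed is a 6-month count in a study that closes at 30 participants, so, read literally, it understates the rate if the study fills in under 6 months (minor)

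*Protocol article*

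**What the plan says.** The protocol article, under Secondary outcomes, Feasibility, names six feasibility outcomes. The one that measures accrual over time is "recruitment speed (number of participants recruited in 6 months".

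The Sample size section fixes the total: "The number of participants was limited to *N* = 30". It adds that "no formal sample size calculation was conducted" and supports the number by a recommendation of "a minimum of 15 participants per group when estimating the variance for a sample size calculation for a future trial". The Randomization section says that the sequence was generated before recruitment began, and that the 30 "participants are randomly assigned to one of the two groups" 1:1.

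The article gives no planned recruitment period, no expected rate, no target for recruitment speed, and no rule for recruitment that ends before 6 months.

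**The concern.** A count over a fixed period measures speed only if recruitment can continue for the whole period. Here recruitment stops when the 30th participant is in, so the count cannot exceed 30. A study that fills quickly and one that just fills in 6 months get the same value, and the outcome cannot tell them apart.

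Accrual rate is one of the things a feasibility study can usefully hand to the planners of a larger trial. If the study fills early and the value is taken at face value, a later trial would be planned on too low a rate and too long a recruitment period.

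**Working it through.** **Inputs.** From the article: a 6-month count (Secondary outcomes, Feasibility), a total of 30 (Sample size, Randomization) and a minimum of 15 per group (Sample size). Assumed: the time taken to fill the study, shown as a range.

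**The plan's own figure.** 2 groups × 15 = 30, which agrees with the stated total. That total is not in dispute.

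**Step 1. The measure as written.** With a constant monthly rate r, the recorded value is min(30, 6r). If the study fills in m months, r = 30 / m.

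| Months to fill (assumed) | Rate per month, 30 / m | Rate per 6 months | Recorded count | Recorded / actual |
|---|---|---|---|---|
| 3 | 10 | 60 | 30 | 0.50 |
| 4 | 7.5 | 45 | 30 | 0.67 |
| 5 | 6 | 36 | 30 | 0.83 |
| 6 | 5 | 30 | 30 | 1.00 |
| 8 | 3.75 | 22.5 | 22.5 | 1.00 |
| 12 | 2.5 | 15 | 15 | 1.00 |

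The understatement is a factor of 6 / m when m is below 6. There is none from 6 months upward.

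**Step 2. Allowing for chance.** Let the uncapped 6-month accrual X be Poisson with mean λ (an assumption). The expected recorded count is E[min(X, 30)], and the cap is reached within 6 months with probability P(X ≥ 30).

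| λ per 6 months | Expected bias | P(cap reached) |
|---|---|---|
| 20 | −0.2% | 2% |
| 25 | −1.8% | 18% |
| 30 | −7.3% | 52% |
| 40 | −25% | 96% |
| 60 | −50% | about 100% |

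The bias is negligible when accrual is clearly slower than 30 in 6 months, modest around that rate, and large only well above it.

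**Step 3. Slow recruitment.** If 30 are recruited over 12 months at 2.5 per month, the 6-month count is about 15. It estimates the rate without bias, but under Poisson accrual its relative standard error is about 1/√15 = 26%, against about 1/√30 = 18% for the full record. This is lost precision, not bias.

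**Step 4. What it could mean for planning.** As an illustration, take the future-trial design that the Sample size section mentions, "designed with 90% power, two-sided 5% significance, and a medium (0.5) effect size". The usual formula gives 2 × (1.960 + 1.282)² / 0.5² = 84.1, so 85 per arm and 170 in total. At the recorded 5 per month, recruitment would be projected at 170 / 5 = 34 months. If the pilot had filled in 5, 4 or 3 months, the projection from the actual rate would be 170 / 6 = 28.3, 170 / 7.5 = 22.7 or 170 / 10 = 17 months.

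**The case against.** The strongest reply is that the harm is conditional. It needs all 30 to be enrolled in under 6 months, and nothing in the article suggests that this will happen. That stands. A reader might infer that the plan will understate the recruitment rate; the document supports only that it would do so if the study fills early.

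A second reply is that the parenthesis may give a unit, participants per 6 months, so that 30 in 3 months would be reported as 60 per 6 months. That reading is possible and removes the ceiling. But the text describes a number recruited, not a rate, and does not say that an early finish is scaled up. One sentence would settle it.

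Third, a reader might infer that the measure is also wrong when recruitment is slow. It is not: a count over a fixed, prespecified period is an ordinary rate measure, and Step 3 shows a loss of precision only.

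Fourth, little depends on the figure. It is a secondary outcome without a threshold, the only stated feasibility criterion is more than 50% of participants providing post-treatment data, and the main analysis is descriptive. The article does not say that a later trial's duration will be projected from it; it mentions a future trial only in connection with estimating the variance. Recruitment dates would let the rate be recovered afterwards, and any error would overstate, not understate, the time a later trial needs. All of this stands and sets the weight. It does not make the definition a good one, since the repair would have to be made after the fact.

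**Conclusion.** The point holds as a minor weakness in a definition. Taken literally, recruitment speed has a ceiling of 30. If the study fills before 6 months, the rate is understated by 6 / m: a factor of 1.5 for an assumed 4 months and 2 for an assumed 3 months. If recruitment takes 6 months or longer, the cap causes no understatement, and the only cost is that later accrual is left out. The fill times, the Poisson model and the 170-participant trial are assumptions for illustration, not figures the article puts forward for this outcome. The primary outcome, the sample size and the feasibility criterion are untouched.

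**What to change.** Under Secondary outcomes, Feasibility, define recruitment speed as the number of participants randomised divided by the months open to recruitment, from the start of screening to the last randomisation. Give an exact confidence interval and report the time to the 30th randomisation. The 6-month count can be kept beside it.

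If recruitment stops at the 30th randomisation after T months, the exact 95% interval under Poisson accrual uses the chi-squared distribution with 2 × 30 = 60 degrees of freedom: 40.48 / (2T) to 83.30 / (2T) per month. For an assumed T = 4 this is 5.1 to 10.4 around 7.5. If recruitment is closed on a calendar date with fewer than 30 participants, the months run to that date and the usual exact Poisson interval applies.

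The cost is one sentence. It needs only the screening start date and the randomisation dates, which any trial records, and changes nothing in the design or conduct of the study.
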